# 1. Introduction

## 1.1 Qualification of Yellow Fever Virus (YFV) molecular assays

World Health Organization (WHO) YF Laboratory Network (YFLN) plays a pivotal role in the surveillance of yellow fever. WHO has chosen to apply a regulatory-based evaluation of commercial sources for molecular assays that detect virus RNA. This evaluation will interrogate the quality as well as the performance of these assays by assessment of the manufacturer’s quality management system, a review of critical verification and validation studies undertaken by the manufacturer (such as stability) and a laboratory-based performance evaluation.

## 1.2 WHO Performance Evaluation of YF Nucleic Acid Tests (NAT)

This document is intended to provide manufacturers of YF NATs and the WHO Evaluating Laboratory with the WHO performance evaluation procedure.

The protocol provides the details of the procedure for the laboratory-based performance evaluation of selected YF molecular assays (also referred to as nucleic acid tests and henceforth in this document as NATs) submitted for evaluation. It describes the procedures required to perform an evaluation of YF NATs submitted for evaluation. **This protocol is not intended to replace validation and verification studies that need to be conducted by the manufacturer.**

The evaluation verifies the performance characteristics of YF NATs, assessing their precision (reproducibility and repeatability), analytical sensitivity, and analytical specificity and clinical performance.

All assays will be performed using a commercially supplied quality control (QC) specimen, and a proficiency panel will be used by all analysts prior to performance evaluation.

Artificially prepared panels will be used to determine precision, inclusivity, analytical sensitivity and specificity. The clinical performance will be evaluated using specimens collected in a YF endemic region during a period of no outbreak. Given the non-availability of YF-positive serum specimens, clinical-like specimens will be generated by spiking serum with a range of concentrations of YFV grown in cell culture. In addition, operational characteristics of the assays will be evaluated, including ease of performance and suitability for use in laboratories within the YFLN.

Testing to evaluate the performance of the NATswill take place at a laboratory with recognised standards accreditation (traceable to ILAC)such as ISO 17025:2017 or ISO 15189:2012 for the performance of NATs.

# 2. Study Objectives

## 2.1 Overall Objectives

The overall objective of the protocol is to evaluate the performance of commercially available YF NATs undergoing WHO assessment.

## 2.2 Specific Objectives:

The specific objectives of the evaluation are to:

- Assess the precision of selected technologies
- Verify claims of limit of detection
- Assess interference and potential for cross-reactions
- Assess detection of different wild type YFV strains from Africa and South America
- Assess relative clinical performance using spiked and unspiked specimens collected during non-outbreak times from the clinical setting where the assay is intended to of used.
- Evaluate the operational characteristics of selected technologies, e.g. ease of performance, specimen type utility
- Report and disseminate the findings of the evaluation.

# 3. Study implementation

## 3.1 Roles and Responsibilities

The performance evaluation will be exclusively conducted by the WHO Evaluating Laboratory. The laboratory will be responsible for the following:

- Ensure availability of the specimen reference panels identified below and maintain their integrity and traceability
- Update specimen inventory
- Conduct testing for the performance evaluation, only using staff with proven competence in the assays under investigation, in accordance with internationally recognized best practices
- Prepare a draft report on laboratory evaluation results, including supervision of the analysis of the data with other YF Laboratory Network members
- Ensure all source data, data analysis records and all correspondence are retained and archived in a detectable manner, for a period of at least ten years
- In addition, the following aspects are key to minimising error and maximising the value of this performance evaluation.

The Principle Investigator of the WHO Evaluating Laboratory, will assume the following responsibilities:

- The Principle Investigator will be responsible for training the laboratory personnel on the details of the evaluation protocol and on the use of each assay undergoing evaluation
- Only those personnel who have received specific training for this evaluation will participate in the evaluation
- Accurate record keeping is crucial to the success of the evaluation and the Principle Investigator will be responsible for ensuring that all data generated by the evaluation are recorded on the agreed data collection sheets, and are accurate and up to date
- It is important to plan work in advance and follow standard operating procedures as prepared and controlled by the Evaluating Laboratory
- Before starting the test run, the operator will prepare worksheets and label all tubes, dilution vessels, test devices or plates with the specimen’s unique number, as appropriate
- It is recommended that any manual transcription involved in testing is checked for correctness by a second operator.

WHO and the YF Evaluation Working Group will assume the following responilibilities:

- Technical advice to the Principle Investigator
- Technical and administrative management of the laboratory evaluation
- Review and verification of the draft report, including seeking of comments on the draft from the manufacturer/s
- Preparation and dissemination of the final reports
- Formal, authorized contacts with the manufacturers
- Ensure publication of the results of these evaluations by WHO and any WHO recommendations derived from the evaluation(s) are be accompanied by the following disclaimer:

*“WHO and the WHO Evaluating Laboratory, do not warrant or represent that the evaluations conducted with the yellow fever NATs referred to in this document are accurate, complete and/or error-free. WHO and the WHO Evaluating Laboratory disclaim all responsibility for any use made of the data contained herein, and shall not be liable for any damages incurred as a result of its use. This document must not be used in conjunction with commercial or promotional purposes.”*

## 3.2 Safety issues

All patient samples could possibly contain other infectious agents like HIV, hepatitis B, C, D, G, E viruses as well as other potential causes of blood borne disease. Therefore, all types of specimens (whole blood, serum/plasma, body fluids, etc.) must be handled as potentially infectious. Appropriate precautions to minimize infectious hazards must be taken at all stages from the collection of specimens to the disposal of waste materials from the laboratory. The WHO Guidelines on HIV Safety Precautions, and Guidelines for the Safe Transport of Specimens (WHO/EMC/97.3) and the site’s guidelines on laboratory safety should be carefully followed by the laboratory staff.

## 3.3 Transportation and Storage of Assays for Evaluation

It is the responsibility of the manufacturer to ensure that the assays are received by the evaluating laboratory in good conditions, according to the instructions for transport and storage provided on the assays.

It is the responsibility of the WHO Evaluating laboratory to ensure all stated storage conditions are maintained after receipt of the assays into the laboratory. Daily records of temperatures shall be kept of all locations where test kits are received. The lot numbers of the test kits received/used, and their expiry dates are recorded on the individual run worksheets.

# 4. Study Design

The study will be conducted with the objective of verifying certain analytical performance characteristics. Although there are many performance characteristics that could be investigated, this evaluation is risk-based and focuses on aspects of greatest importance to assuring the safety and performance when such IVDs are used in WHO Member States.

Apart from where the YF NAT is part of a closed system, all specimens will be processed and tested using an extraction kit and thermocycler which are recommended by the manufacturer. Since the Qiagen QIAamp Viral RNA Mini Kit and the Applied Biosystems ABI 7500 are the extraction kit and thermocycler most commonly in place in the YF Laboratory Network, these should be part of the evaluation.

Analytical aspects that will be evaluated include the following performance characteristics:

## 4.1 Precision of measurement

- Intra-assay variation within a run (repeatability)
- Inter-assay variation between runs performed on three different days using different technicians (within-laboratory precision/reproducibility)
- Inter-lot variability based on testing of two independent lots of the product

## 4.2 Analytical Sensitivity

- Limit of detection (LoD)
- Inclusivity - Detection of African and South American wild type YFV strains

## 4.3 Analytical Specificity

- Reactivity with other flaviviruses
- Reactivity with other pathogens likely to be encountered in regions with YF.
- Reactivity with potentially interfering or inhibiting endogenous substances

## 4.4 Clinical Performance

- It is acknowledged that use of natural clinical specimens is preferable for a clinical evaluation.
- In the absence of known positive specimens available for testing, the clinical performance will consist of testing a series of YFV-negative clinical specimens spiked with YF virus in a randomized blinded fashion.

## 4.5 Usability Assessment

- Technicians with known skill in molecular assay performance will complete a questionnaire that include questions about the ease of use for the procedure including
- specimen and reagent preparation
- clarity of instructions for use
- record of any specific difficulties encountered or requirements

# 5. Specimen Panels

## 5.1 Specimen types

All panels will be prepared using the specimen type/s indicated in the NAT’s instructions for use. Where multiple specimen types are identified, serum will be the preferred specimen type. The clinical specimens will be serum collected from an endemic setting during a non-outbreak period. Where possible, specimens should be collected from patients with symptoms similar to those seen in YF.

## 5.2 Specimen Preparation

All personally identifying information of specimens used in the performance evaluation will be delinked from the specimen, with consequent labelling providing a link to results, not patient.

After removal of all the patient-specific identifiers, the specimens will be assigned a unique identification number for transport purposes and an agreed volume sent to the Evaluation Laboratory where they will be assigned the specimen identification number.

## 5.3 Specimen Shipping and Transport

Specimens are to be shipped to the evaluating laboratory using dry ice and will be stored at
-20°C (or preferable at -80°C if available) until use. During the period of testing the specimen aliquots will be stored at 4- 8°C for no longer than three days. To avoid frequent freeze/thaw cycles samples should be stored in aliquots. After the completion of testing, remaining volume of specimens will be stored at -20°C. Each aliquot should not undergo more than two freeze/thaw cycles. A system to monitor the sample handling shall be implemented.

## 5.4 Analytical Performance Specimen Reference Panel

Reference Panel preparation consists of cell culture-grown YF strains (17D YF vaccine strain, prototype African wild type strain, prototype South American wild type strain) diluted in YF negative serum.

The YF 17D standard preparation (RKI / European Virus Archive (EVA), <https://www.european-virus-archive.com/node/2495>) could be used as 17D reference material. Also the EQA YF Virus 195 panel from QCMD could be used as reference material. This panel comprises YFV 17D in different concentrations, Japanese encephalitis, West Nile, Zika, and Dengue 2 viruses for analysing the assay specificity.

- Precision of measurement:
- Three specimens representing the most relevant YFV strains (17D YFV vaccine strain, African wild type strain, South American wild type strain) will be used. Each YFV-positive specimen will be diluted in serum which has been tested negative for HIV, HBV and HCV to obtain a concentration of ca. 5000 ge copies / mL of the assay.
- Inclusivity:
- Specimens to demonstrate appropriate YF strain detection. They should comprise at least the 17D YFV vaccine strain, an African wild type strain and, a South American wild type strain. These specimens will be diluted to a concentration of 5000 ge copies/mL of the assay.
- Assessment of the Analytical sensitivity:
- The YFV 17D standard preparation from RKI will be used to prepare five-fold serial dilutions in YFV-negative serum comprising at least two concentrations at 5000 ge copies /mL, one concentration at 1000 ge copies /mL and two concentrations at 500 and 100 ge copies/ mL (Tab. 1)
- Analytical Specificity
- Non-YFV flavivirus strains and other pathogens (except malaria). Testing will be conducted with cell culture preparations of the various viruses (using prototype strains) spiked into negative serum specimens. Each virus will be spiked at concentrations found in clinical presentations.
- Interfering substances.
- Testing will be conducted with YFV 17D standard preparation at a concentration of ca. 10^3^ ge copies/mL spiked with challenging sera (see Table 1) in order to detect potential interference for the assays under evaluation. The malaria specimens will be those identified as positive by microscopy.

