## 5.5 Clinical performance panel

- Left-over whole blood or serum submitted for routine testing can be used to evaluate the assays. Clinical specimens should be stored frozen at -20°C or preferable -80°C when available until testing. Total 100 specimens: 10 spiked with 5000 ge /mL of the African wild strain, 10 spiked with 5000 ge /mL of the South American wild strain and 80 non-reactive specimens will be tested.

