### Table 1: Assay Performance Specimen Reference Panel

| **Analyte - Sample type** | **Concentration (copies/mL)** | **N° of replicates** | **Total N° replicates** |
| --- | --- | --- | --- |
| **Precision of measurement and inclusivity** |  |  |  |
| **Intra-assay precision/inclusivity** |  |  |  |
| YF 17D vaccine strain* | Each strain will be diluted at a concentration of ca. 10^3^, 10^4^ and 10^5^ ge copies /mL and run in quadruplicate | 3 | 12 |
| African wild type strain* |  | 3 | 12 |
| South American wild type strain* |  | 3 | 12 |
| **Inter-assay precision** |  |  |  |
| YF 17D vaccine strain* | Each strain will be diluted at a concentration of ca. 10^3^, 10^4^ and 10^5^ ge copies /mL and run in quadruplicate on 3 different days by different technicians (day 1 can use intra-assay data) | 3 | 24 |
| African wild type strain* |  | 3 | 24 |
| South American wild type strain* |  | 3 | 24 |
| **Inter-lot variability** |  |  |  |
| YFV 17D vaccine strain* | Each strain will be diluted at a concentration of ca. 10^3^, 10^4^ and 10^5^ and run in quadruplicate | 3 | 12 |
| YFV African wild type strain* |  | 3 | 12 |
| YFV South American wild type strain* |  | 3 | 12 |
| **Analytical Sensitivity** | | | |
| YFV Standard preparation* | ca. 10, 50, 100, 500, 1000, 5000, 10^4^, 5x10^4^, 10^5^, 5x10^5^, 10^6^ , 5x10^6^ ge copies /mL** | 5 | 25 |
| **Analytical Specificity (**Flavivirus strain detection) | | | |
| Hepatitis C* virus | Medium concentration  ca. 10,000 ge copies/mL | 1 |  |
| Dengue 1, 2, 3, 4*virus |  | 1 |  |
| Zika virus* |  | 1 |  |
| West Nile virus* |  | 1 | 9 |
| Tick Borne Encephalitis virus* |  | 1 |  |
| Japanese Encephalitis virus* |  | 1 |  |
| **Analytical Specificity (other pathogens)** | | | |
| Ebola virus* | medium concentration  ca. 10,000 ge copies/mL | 1 |  |
| Lassa fever virus* |  | 1 |  |
| Marburg virus* |  | 1 |  |
| HIV* |  | 1 | 8 |
| Hepatitis E virus* |  | 1 |  |
| Chikungunya virus* |  | 1 |  |
| Measles virus* |  | 1 |  |
| Influenza virus* |  | 1 |  |
| **Analytical Specificity (interfering substances)** | | | |
| Haemoglobin | 200 g/L | 3 |  |
| Triglyceride | 5.6 mmol/L | 3 | 12 |
| Bilirubin (unconjugated) | 257 µMol/L | 3 |  |
| Malaria positive sera |  | 3 |  |
| **Clinical Performance Panel** | | | |
| Non-reactive serum specimens Spiked African wild type | 5000 ge copies/ mL | 10 | 10 |
| Non-reactive serum specimens Spiked South American wildtype | 5000 ge copies/ mL | 10 | 10 |

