| Non-reactive serum specimens |  | 80 | 80 |
| Total number of samples to be | tested |  | 305 |

ge = genome equivalent

* A inactivated YF prototypevirus grown in cellculture should be used for this evaluation.

All specimens will be prepared in concentrations representing the dynamic range of the assay under evaluation.

**Five of these dilutions will be chosen where the manufacturer’s LoD is approximately the middle dilution

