**6.2 Analytical Performance Testing**

The determination of precision and inclusivity will be undertaken in a single set of experiments.

- Four specimens will be used: one YF negative, one YF 17D, one YF African wild type, and one YF South American wild type, at a concentration of 10^3^-10^5^ ge copies /mL, (see Table 1).
- Intra-run variability (repeatability): The same sample panel (ca.10^3^, 10^4^, 10^5^ ge copies/mL) should be tested on the same run. Each panel member should be tested in quadruplicate.
- Inter-run variability (reproducibility): The same sample panel (ca. 1000, 10^4^, 10^5^ ge copies/mL) should be tested in 3 different runs preferably by different technicians.Each panel member should be tested in quadruplicate on each run.
- Inter-lot variability: The same sample panel (ca.10^3^, 10^4^, 10^5^ ge copies/mL) should be tested on a second lot of the product. Tests should be performed in quadruple.

Results should not vary by more than 3 ct values, by frequent performance in the same laboratory.

Twelve concentrationss of YF 17D standard preparation, diluted as described in Table 1, will be tested 5 times. The 5 replicates will be separated in a minimum of three runs where applicable.

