## 6.4 Clinical Performance

All specimens will be tested in singlicate in a randomized blinded fashion.

The acceptance criteria for the performance as 95% agreement at 1000 ge copies / mL, and 100% agreement at all other higher concentrations and for negative specimens.

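### Section 5.4 prepares the precision and inclusivity specimens at one level, 5000 ge/mL, while Table 1 and section 6.2 test them at 10^3, 10^4 and 10^5 ge/mL

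*Protocol*

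**What the plan says.** Section 5.4 describes how the analytical panel is made. For precision, each of the three strains is diluted in serum "to obtain a concentration of ca. 5000 ge copies / mL of the assay". For inclusivity, the same three strains are named and the text reads: "These specimens will be diluted to a concentration of 5000 ge copies/mL of the assay". Each use therefore has one level.

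Table 1 has a block for precision and inclusivity together. Its entry reads: "Each strain will be diluted at a concentration of ca. 10^3^, 10^4^ and 10^5^ ge copies /mL and run in quadruplicate". The inter-assay and inter-lot rows carry the same three levels. The total replicates per strain are 12 (intra-assay), 24 (inter-assay, where day 1 may reuse the intra-assay data) and 12 (second lot).

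Section 6.2 says: "The determination of precision and inclusivity will be undertaken in a single set of experiments". It repeats the three levels for the intra-run, inter-run and inter-lot comparisons and refers to Table 1.

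**The concern.** Section 5.4 is where the specimens are specified, so staff preparing them may well work from it. Section 6.2 is where the runs are specified. The two give different specimens for the same experiment, and 5000 ge/mL is not one of the three levels in Table 1.

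Two things are at stake if section 5.4 is followed. First, precision, including the limit of 3 Ct in section 6.2, would be judged at one concentration instead of across a hundredfold range. Second, detection of African and South American wild-type strains is a stated objective (section 2.2), and the low level of the precision and inclusivity block is where Table 1 tests those strains at 1000 ge/mL. Assays evaluated under different readings would also not be comparable.

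**Working it through.** **1. Can the two versions be reconciled?**
- As separate experiments: no. Section 6.2 runs precision and inclusivity together, and section 5.4 gives 5000 ge/mL for each of them.
- As a stock concentration: no. Levels of 10^4 and 10^5 cannot be reached by diluting a specimen at 5000.
- Through the Table 1 note, "All specimens will be prepared in concentrations representing the dynamic range of the assay under evaluation": no. It names no level and does not choose between the two.

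**2. Which version do the counts support?** Inputs from Table 1: 3 strains, 4 replicates per level, and 1 intra-assay run, 2 further days and 1 run on the second lot.

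Per strain, levels × 4 × runs:

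| | Three levels | One level | Table 1 |
|---|---|---|---|
| Intra-assay | 3 × 4 × 1 = 12 | 1 × 4 × 1 = 4 | 12 |
| Inter-assay | 3 × 4 × 2 = 24 | 1 × 4 × 2 = 8 | 24 |
| Inter-lot | 3 × 4 × 1 = 12 | 1 × 4 × 1 = 4 | 12 |

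The three-level design reproduces Table 1's totals per strain exactly.

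Precision block over 3 strains:
- Three levels: 3 × (12 + 24 + 12) = 144.
- One level: 3 × (4 + 8 + 4) = 48. Section 5.4 gives no replicate numbers, so this borrows Table 1's.

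Remaining Table 1 rows: 25 (analytical sensitivity) + 9 + 8 + 12 (specificity) + 100 (clinical) = 154.

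All rows:
- Three levels: 144 + 154 = 298.
- One level: 48 + 154 = 202.

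The stated totals are 305 (Table 1) and 310 (section 10). The three-level sum is 7 and 12 short of these; the one-level sum is 103 and 108 short. The totals favour three levels but do not confirm them exactly.

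**3. Where does Table 1 test wild-type virus at 1000 ge/mL?**
- Analytical sensitivity: 17D standard only.
- Interfering substances: 17D only.
- Clinical panel: "10 spiked with 5000 ge /mL of the African wild strain, 10 spiked with 5000 ge /mL of the South American wild strain", so none at 1000.
- Precision and inclusivity, three levels: 4 + 8 + 4 = 16 replicates per strain at 10^3, or 32 for the two wild types.
- Precision and inclusivity under section 5.4: 0.

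**4. What remains outside Table 1?** The proficiency panel (section 7.3) has 10 specimens: 3 strains × 3 levels + 1 negative = 10. That is one specimen of each wild type at 1,000 ge/mL, run by each operator before the evaluation starts.

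**The case against.** The best defence is that the harm is unlikely to occur. Section 6.2 repeats the correct levels for each precision component and points to Table 1, so a laboratory that works from section 6 runs the intended design. That is fair, and it is a reason to rate the point as minor. It does not remove the conflict, because section 5.4 governs what is in the tubes.

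It can also be said that only the intra-assay sub-heading of Table 1 names inclusivity. On that narrow reading the inclusivity evidence at 10^3 is 4 replicates per strain, not 16. The block heading covers both uses, and all 16 are wild-type tests at that level. On either reading section 5.4 leaves none.

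A reader might infer three stronger claims. The protocol does not support them.
- *That the listing gate would be weakened.* The section 8.3 criterion (LoD at or below 1000 ge/mL) is tested with 17D only, whichever version is used. No pass rule for detection is tied to the inclusivity rows; the only limit in section 6.2 is the 3 Ct limit on variation.
- *That the conflict leaves the section 6.4 criterion without specimens.* That criterion, "95% agreement at 1000 ge copies / mL, and 100% agreement at all other higher concentrations and for negative specimens", is set for the clinical panel. The clinical panel has no specimen at 1000 ge/mL under either version, so this is a separate defect that correcting section 5.4 does not cure.
- *That the loss can be expressed as the chance of wrongly passing an assay.* One could assume a detection curve and compute the chance that all replicates are positive. The protocol states no such curve and no all-detected rule. Under an assumed single-hit curve, an assay with a wild-type LoD of exactly 1000 would give 16 of 16 positive with probability 0.95^16 = 0.44, so such a rule would fail that assay more often than not.

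**Conclusion.** The contradiction is real and lies in the current text. Section 5.4 is almost certainly the part in error, because Table 1's totals per strain fit only the three-level design.

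The consequence is conditional on a laboratory preparing specimens from section 5.4. In that case precision would be assessed at one level, and Table 1's wild-type evidence at 1000 ge/mL would fall from 16 replicates per strain to none, leaving only the operator proficiency panel. The loss is one of reported evidence on wild-type detection at low concentration, and no listing decision rule changes. The figure of 16 assumes that day 1 of the inter-assay series reuses the intra-assay data, as Table 1 allows and as its total of 24 implies. Severity: minor.

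**What to change.** In section 5.4, replace 5000 ge/mL with ca. 10^3, 10^4 and 10^5 ge/mL in two places, the precision item and the inclusivity item, to agree with Table 1 and section 6.2. The 5000 ge/mL clinical spikes and the Table 1 note on dynamic range need no change on account of this point.

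The cost is wording only. No extra tests are needed, because Table 1's row totals already count three levels. The one downside, which falls on manufacturers, is a less favourable reported result for an assay that is weak on wild-type strains at low concentration.
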